**Independent Data Collection System**

An independent data collection system will be established through trained research data collectors in addition to the baseline and endline assessments for the regular operational monitoring of project outcomes.

**Recruitment of potential participants:**

Children 6-23 and 24-59 months of age and Pregnant or lactating mothers will be potentially eligible cohorts for inclusion in the study and will be identified through the baseline survey being done in the targeted union councils. Pregnant women will be enrolled during first and second trimester of pregnancy, children 6-23 months cohort during 6-18 months and children 24-59 months cohort during 24-54 months of age for minimum exposure of six months. A detailed recruitment form will be filled from each study participant. Detailed physical & anthropometric examination and sport Hb testing will also be done at the time of recruitment.

**Monthly follow-up for compliance assessment:**

The project team will also conduct monthly follow ups of the recruited children and PLW for the assessment of compliance of the commodities. The compliance will be assessed via observation of used packets of commodities and parental recall.

**Quarterly Surveillance for monitoring of process and outcome indicators:**

The independent project team will conduct a quarterly (every three months) surveillance of the recruited children and PLW for the detailed anthropometric examination, compliance assessment, hemoglobin testing and programme related data at household level. This surveillance will enable to monitor the linear growth of children and its relationship with the intervention. Temporal trends of malnutrition will be the main outcome of this surveillance system. Over a period of one year intervention there will be four surveillance rounds.

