**Objectives of impact assessment of Stunting Prevention Project by AKU**

The broad objectives of the research component of the project are:

1. To assess the effectiveness of the food/nutrient -based interventions on reduction of stunting among children under two.
2. To assess the effectiveness of the food/nutrient-based interventions on reducing stunting and micronutrient deficiencies in children 6-59 months.
3. To assess the effectiveness of the food/nutrient-based interventions on reduction of wasting and anemia in pregnant and lactating women and an impact on the birth outcome (reduce low birth weight),
4. To assess the design and operational factors at the different stages of the programme cycle that may have affected the outcome.
5. To determine unintended consequences of the interventions, both positive and negative.
6. To determine cost-effectiveness.
7. To provide recommendations for improved programme design and evaluation.
8. To know the optimal length of preventive intervention.
9. To compare the use of specialized nutritious foods over other interventions, such as conditional cash transfers for stunting prevention.

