**B. Impact Assessment of the Project:**

**Nested Cluster Randomized Controlled Trial**

During intervention delivery, a randomized controlled trial will also be conducted on a sub-set of targeted subjects for further robustness and to get the in-depth evidence about the impact of interventions on health and nutrition outcomes.

The Aga Khan University proposes an embedded Cluster Randomized Controlled Trial for more robust evaluation of the intervention being carried out by WFP. This CRT will be done at union council level to assess the acceptability, feasibility and effectiveness of food based interventions to prevent stunting among children in community settings. The project will utilize the window of opportunity (1000 days from conception to 2 years) for addressing stunting in children under-five years. Therefore project will recruit three types of cohorts in the study i.e. children 6-23 months, children 24-59 months and pregnant women to follow the newborns who delivered from recruited pregnant women.

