**Collection of Blood Samples:**

About 3-cc blood samples will be collected from 500 children during 6-8 months of age and at 24 months of age from cohort of pregnant women and lactating mother’s group. The purpose of blood collection is to assess micronutrient deficiencies and impact of intervention in children. Children will be selected from both intervention and control areas after getting informed consents from their parents. This will enable us to compare improvements across intervention and control groups.

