**Cost Effectiveness Analysis**

Cost effectiveness analysis will run through the full three years of the program. For our analysis we will have 2 arms whose cost effectiveness will be compared: Arm 1: food based and preventive health interventions; Arm 2: preventive health interventions only. The time frame for both will be three years of intervention

To be able to assess the cost effectiveness of the intervention and control arms current, we will compare interventions with a scenario of doing nothing to improve child health. Incremental cost effectiveness ratios will be computed for each arm by calculating the incremental improvement over Do Nothing scenario.

A sensitivity analysis will be carried out to report results with or without 3% discounting for DALYs and using cost inputs for foreign prepared versus locally prepared supplements.

*Cost Calculation:* Unit costs for provision of food supplements and for delivery of preventive health measures will be developed based on programmatic records. A record of program inputs and costs will be maintained during the length of the program and verified by an external accountant. 2013 as the base year will be kept as the base year with costs converted to 2013 purchasing power parity to remove the effect of inflation. All costs will be summarized in US dollars and future costs discounted at 3%.

*Effect Calculation*: Percent reduction in stunting will be taken as the effect outcome. Efficacy will be obtained through Before After household survey. Changes in linear growth will also be calculated.

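### The one-year, four-round trial follow-up conflicts with the planned 24-month blood sample and the three-year time frame; separately, the design cannot support objectives 8 and 9 or all of objective 2's micronutrient claim

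*Protocol*

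**What the plan says.** **Duration.** In the Protocol, *Quarterly Surveillance for monitoring of process and outcome indicators* provides for "quarterly (every three months) surveillance of the recruited children and PLW" and then states: "Over a period of one year intervention there will be four surveillance rounds". *Nested Cluster Randomized Controlled Trial* places the project in the window from conception to age two and recruits "pregnant women to follow the newborns who delivered from recruited pregnant women". Under *Recruitment of potential participants*, "Pregnant women will be enrolled during first and second trimester of pregnancy", and lactating mothers are also named as eligible. *Collection of Blood Samples* plans draws from 500 children at 6-8 months "and at 24 months of age from cohort of pregnant women"; that sentence goes on to include the lactating mothers' group. The survey sample-size section refers to a three-year programme. *Cost Effectiveness Analysis* says of its two arms: "The time frame for both will be three years of intervention".

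**Objectives.** The AKU objectives include item 8, "To know the optimal length of preventive intervention", and item 9, "To compare the use of specialized nutritious foods over other interventions, such as conditional cash transfers for stunting prevention". *Key Questions* lists the lengths to choose between: 6-12, 6-18 or 6-23 months, and 24-30, 24-36, 24-48 or 24-59 months. Item 2 covers stunting and micronutrient deficiencies at 6-59 months.

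**Design.** Each age band gets one product for the whole programme period (*Study Site and eligibility criteria*). The trial has two arms of six union councils each, and control clusters receive routine services.

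**The concern.** A child whose mother enters the trial while pregnant spends part of the follow-up unborn. One year from enrolment therefore looks too short for a sample at the second birthday. If so, the only cohort followed from pregnancy would stop well before age two, and the micronutrient comparison at 24 months would not exist.

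Three objectives raise a different question, which does not depend on duration: whether any planned comparison or measurement can answer them. An objective with no matching arm or assay tends to be answered later by whatever comparison is available, and may then be read as if the trial had been designed for it.

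**Working it through.** **Inputs from the Protocol**
- Trial follow-up 12 months, one round every 3 months (*Quarterly Surveillance*).
- Enrolment in trimester 1 or 2; child cohorts enter at 6-18 and 24-54 months (*Recruitment*).
- Lactating women are eligible in the first six months after birth, so their infants are 0-6 months old at entry (*Study Site and eligibility criteria*).
- Blood at 6-8 and 24 months (*Collection of Blood Samples*).

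**Assumptions (not in the Protocol)**
- Entry at 6 to 27 weeks of gestation and delivery at 40 weeks; 4.348 weeks per month.
- The year is counted from each participant's own enrolment. A calendar year would give late entrants less.

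**1. The plan's own figure.** 12 / 3 = 4 rounds, so the sentence agrees with itself at one year.

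**2. Children of women enrolled in pregnancy.** Months to birth = (40 − weeks at entry) / 4.348.

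| Entry (weeks) | Birth at month | Age at month 12 | Turns 6 months at | Turns 24 months at | Quarterly rounds needed |
|---|---|---|---|---|---|
| 6 | 34/4.348 = 7.8 | 4.2 | 13.8 | 31.8 | 11 |
| 13 | 27/4.348 = 6.2 | 5.8 | 12.2 | 30.2 | 11 |
| 20 | 20/4.348 = 4.6 | 7.4 | 10.6 | 28.6 | 10 |
| 27 | 13/4.348 = 3.0 | 9.0 | 9.0 | 27.0 | 9 |

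At month 12 these children are 15 to 20 months short of 24 months. Those whose mothers entered by 13 weeks have not yet reached the first (6-8 month) sampling age.

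**3. Infants of lactating mothers.** Age at month 12 is 0 + 12 = 12 to 6 + 12 = 18 months. They turn 24 months at 24 − 6 = 18 to 24 − 0 = 24 months after entry. None reaches 24 months within a year.

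**4. If three years were meant.** Entry at 6 weeks must happen by month 36 − 31.8 = 4.2, and entry at 27 weeks by month 36 − 27.0 = 9.0. The sample is then feasible, but only with early enrolment.

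**5. Feeding length (objective 8).** Counting each band to its end, the candidates last 6, 12 and 18 months for infants, and 6, 12, 24 and 36 months for older children. Three of the seven (6-23, 24-48, 24-59) exceed 12 months. Possible exposure for an infant entering at age *a* is:
- One year: min(12, 24 − *a*). This is 12 months for entry at 6 to 12, 9 for entry at 15, and 6 for entry at 18.
- Three years: 24 − *a*. This is 18 months for entry at 6 and 6 for entry at 18.

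Either way, entry age fixes the available exposure, so a comparison of lengths is confounded with age. More follow-up widens the range but does not break the link.

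**6. Cash transfers (objective 9).** The trial compares supplements with routine services. The cost-effectiveness section compares food plus preventive health with preventive health alone, each against doing nothing. Arms with cash: 0 of 2.

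**7. Micronutrients (objective 2).** Venous blood is planned only in the pregnant and lactating women's cohort, at 6-8 and 24 months. For the 24-59 month cohort, recruitment and quarterly rounds provide haemoglobin only. The surveys also provide only haemoglobin and clinical signs of anaemia, and the secondary outcomes name no other micronutrient measure.

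**The case against.** **One year may be loose wording.** The surveillance sentence could mean four rounds in each year of a longer programme, and a planned 24-month sample itself suggests longer follow-up. The blood section does not tie its draws to the rounds. The three-year figures describe the programme and the cost analysis, so a one-year trial inside a three-year programme is also conceivable. This stands as far as it goes: it is too strong to say flatly that the trial cannot obtain the 24-month sample. But the text does not say which reading is meant, and the answer changes the pregnancy cohort's follow-up from 4 rounds to 9-11.

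**Objective 1 does not depend on the birth cohort.** A reader might infer that stunting under two goes unanswered. The Protocol does not support that. Objective 1 specifies neither age 24 months nor exposure from pregnancy. The trial has its own 6-23 month cohort of 900 children sized on stunting, the surveys are sized on stunting, and the pregnancy cohort is sized on low birth weight, which is observed at delivery and so within a year.

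**Objective 8 promises no randomised comparison of lengths.** True. Quarterly growth, growth velocity and monthly compliance in both arms do allow supplement-control contrasts after 3, 6, 9 and 12 months. Those show how an effect builds up. They do not compare stopping earlier with continuing to a common later age, which a recommended length requires.

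**Objective 9 gives cash only as an example.** Also true, and the surveys record the existence and coverage of other interventions. That could support an observational description, although cash is not named there.

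**Conclusion.** The concern holds in a limited form. Read literally, the one-year follow-up contradicts the 24-month blood sample for every child in the cohort to be sampled. The time needed is about 27 to 32 months from enrolment in pregnancy, or 18 to 24 months for infants of lactating mothers; the longer figure should not be applied to both groups. No gestation within the first two trimesters changes this. What is at risk is the 24-month micronutrient result and the birth-cohort evidence for the first 1000 days. The main supplement-versus-control comparison and objective 1 survive.

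The other three gaps are independent of duration. Objective 8 has no assigned feeding length, objective 9 has no cash arm, and objective 2's micronutrient claim goes beyond haemoglobin in an age group where only haemoglobin is measured. It would be wrong to blame the cash-transfer gap on short surveillance, since longer follow-up would not supply an arm. These are design matters fixed in the Protocol, and an analysis plan cannot create a missing arm or an unvisited age. They should be corrected, mainly because they limit what the trial may conclude.

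**What to change.** - Reconcile the duration statements in the survey sample-size, *Quarterly Surveillance*, *Collection of Blood Samples* and *Cost Effectiveness Analysis* sections. Either state follow-up that covers the 24-month sample for both the pregnant and the lactating women's children, or drop that sample and the claim resting on it.
- If the sample is kept, record length at the same visit, so that the birth cohort also yields growth data at age two.
- Restate objective 8 and the matching key questions as descriptive and non-randomised, with exposure length tied to entry age.
- Delete objective 9, or restate it as exploratory and observational.
- Limit objective 2's micronutrient claim to the ages at which blood is drawn, with haemoglobin and anaemia only for the 24-59 month cohort.

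The cost is mostly wording, plus one length measurement at a visit already planned. Extra surveillance rounds cost money only if the longer period is not already funded; the Protocol text available gives no budget from which to judge that.

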**Collection of Blood Samples:**

About 3-cc blood samples will be collected from 500 children during 6-8 months of age and at 24 months of age from cohort of pregnant women and lactating mother’s group. The purpose of blood collection is to assess micronutrient deficiencies and impact of intervention in children. Children will be selected from both intervention and control areas after getting informed consents from their parents. This will enable us to compare improvements across intervention and control groups.

**Outcome Measures:**

**Primary Outcome Measure:**

The primary outcome will be reduction in risk of stunting in intervention group compared with control group.

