## Study Site and eligibility criteria

According to the implementation plan of WFP, the project will be operating in 29 Union Councils (UCs) in Thatta and Sajawal districts. The UCs were selected on the basis of LHW´s presence, since they are the main implementing partners. The project aims to reach children 6-23 months, children 24-59 months and PLW.

Inclusion criteria for children and mothers are defined as follows:

**Children 6-23 months:** All eligible children between 6-23 months in the catchment area will be enrolled for food supplements, independent of nutritional status and age. This group will receive Wawamum during the programme period.

**Children 24-59 months:** All eligible children between 24-59 months in the catchment area will be enrolled for food supplements, independent of nutritional status and age. This group will receive MNPs during the programme period.

**Pregnant and lactating women:** All pregnant women will be enrolled in the project, regardless of the month of pregnancy and nutrition status. The programme will try as much as possible to engage women at earliest stage of the pregnancy. Similarly all lactating women in the first six months after giving birth will be engaged, covering the exclusive breastfeeding period. It is also being discussed whether it will be important a screening to identify overweight or obese women and what would be the approach in such cases.

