**Sample size and design for Baseline and End line Surveys**

Clearly it would be impossible to conduct an in-depth evaluation of all population in the community based nutrition program. However, the assessment must be robust, scientifically valid and plausible within existing time frames. Therefore a representative sample size has been calculated separately for both baseline & endline surveys and embedded Randomized control trial. Details of both estimations are as under:

Below mentioned formula for sample size estimation for baseline and endline cross sectional surveys were used from MI & CDC manual [6] to calculate the sample size. Prevalence of stunting (49% Sindh) from NNS 2011, 80% power to detect 10% reduction in prevalence of stunting during the three-year implementation of the Stunting Prevention Programme with a significance level of 0.05 was considered for sample size estimation.

[figure not shown]

Assumptions:

- p1 is stunting rate at baseline without intervention at baseline survey =49%
- p2 is estimated stunting rate after intervention at end line survey
- DEFF : The estimated design effect = 1.5
- α : Level of significance (“alpha”), usually 0.05 or 5% (corresponds with 95% confidence interval)
- 1- β: Power, usually 0.8 (80%) Assumed 10% reduction in stunting

For estimating impact of the interventions each group will require 3200 participants. To account for dropouts and data errors, the sample size will increased by 10% giving a new total of 7040 study participants (3520 participants per group). Information will be collected from 4,200 households at baseline and at endline. The study participants from selected households will be pregnant women, lactating women and children under five years. Two stage cluster sampling technique will be used. LHW catchment areas of 29 UCs will be treated as a cluster for intervention group and control group.

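### The trial's primary outcome, risk of stunting, makes no use of stunting status at recruitment, although 44-49% of under-fives in the cited populations are stunted; adjusting for recruitment height-for-age is a cheap gain in precision and clarity

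*Protocol*

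**What the plan says.** The Primary Outcome Measure section reads, in full: "The primary outcome will be reduction in risk of stunting in intervention group compared with control group". It gives no time point and no cut-off. It does not say whether risk means new cases or prevalence, and it does not mention status at entry.

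The trial's stated aim is to assess "effectiveness of food based interventions to prevent stunting among children in community settings" (Nested Cluster Randomized Controlled Trial). Programme eligibility does not depend on nutritional status: "All eligible children between 6-23 months in the catchment area will be enrolled for food supplements, independent of nutritional status and age", with the same rule for the older group (Study Site and eligibility criteria). The trial recruits the "children 6-23 months cohort during 6-18 months and children 24-59 months cohort during 24-54 months of age for minimum exposure of six months" and excludes no child for stunting. A third cohort consists of "pregnant women to follow the newborns who delivered from recruited pregnant women".

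Height at entry will be known: "Detailed physical & anthropometric examination and sport Hb testing will also be done at the time of recruitment" (Recruitment of potential participants). The Data Analysis section announces univariate and multivariate methods, but the only test it names is Pearson's chi-square for categorical variables.

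Two stunting prevalences are given: 44% of under-fives nationally (Preamble) and 49% for Sindh, used for the surveys: "p1 is stunting rate at baseline without intervention at baseline survey =49"%. The trial's own sample-size paragraph states no control risk.

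**The concern.** A child who is already stunted at recruitment cannot have stunting prevented during the year; that child can only recover or stay stunted. If the primary comparison is the proportion stunted at the last round among all children, much of what it counts was fixed before follow-up began. Two things follow.

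- **Precision.** With six clusters per arm, the arms will differ by chance in entry stunting. An unadjusted comparison leaves that noise in the result, although the height measured at recruitment could remove part of it.
- **Interpretation.** A lower final prevalence could come from fewer new cases or from more recoveries. These lead to different conclusions for a prevention programme and for the protocol's question about optimal length of feeding.

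**Working it through.** **Inputs from the protocol.** Six clusters per arm; 70-75 children per cluster aged 6-23 months (900 in total) and 90-95 aged 24-59 months (1,100 in total); intra-cluster correlation (ICC) 0.02; alpha 0.05; power 0.80; a 10% difference in stunting, not stated as absolute or relative; prevalence 44% or 49%; one year with four quarterly rounds.

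**The plan's own figure.** The totals fit the cluster counts: 900/12 = 75 and 1,100/12 = 91.7. The cluster sizes do not follow from the 49% prevalence. A fall from 49% to 39%, two-sided, needs 386 children per arm before clustering. With six clusters the size m solves m = n(1 - ICC)/(6 - n x ICC), and 386 x 0.02 = 7.7 exceeds 6, so no cluster size reaches 80% power. By the normal approximation the stated sizes give about 47-48% and 51-52%. With the ICC, a 10-point fall from a control risk of 18% gives 70.5 per cluster, and from 20% gives 96.5. Those risks look more like new-case risks than prevalences, but the protocol does not say which was meant.

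**Share of final events already present at entry.** Let p0 be the proportion stunted at entry, r the recovery among them, and q the new stunting among the rest. Then

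share = p0(1 - r) / [p0(1 - r) + (1 - p0)q].

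The protocol gives neither r nor q. The assumed ranges are r = 0 to 0.30 and q = 0.05 to 0.30.

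| p0 | Lowest (r = 0.30, q = 0.30) | Highest (r = 0, q = 0.05) |
|---|---|---|
| 0.44 | 0.308/(0.308 + 0.168) = 65% | 0.440/(0.440 + 0.028) = 94% |
| 0.49 | 0.343/(0.343 + 0.153) = 69% | 0.490/(0.490 + 0.0255) = 95% |
| 0.30 | 0.210/(0.210 + 0.210) = 50% | - |

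A second route treats height-for-age z-score (HAZ) at entry and at the final round as bivariate normal with an assumed correlation of 0.6-0.9. It gives 67-84% at 44% and 70-85% at 49%. At 49%, new stunting is then 14-29% of those not stunted at entry.

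**Chance difference in entry prevalence between arms.**

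SD = sqrt{2 x 0.49 x 0.51 x [1 + (m - 1) x 0.02] / (6m)}

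- m = 73: sqrt(0.4998 x 2.44/438) = 0.053
- m = 92: sqrt(0.4998 x 2.82/552) = 0.051

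This is about half of an absolute 10-point effect.

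**How much carries through.** At the individual level the fraction is (1 - r) - q. With prevalence stable at 49% and shares of 70% and 85%, it is 0.70 - 0.29 = 0.41 and 0.85 - 0.14 = 0.71. Union-council levels that persist over the year raise it, to about 0.64-0.77 at a persistence correlation of 0.8. If they do not persist at all it is about 0.15-0.3.

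**Power with and without adjustment.** Simulated trials used 49% v 39%, six clusters per arm, 73 or 92 children per cluster, ICC 0.02 and entry-to-final HAZ correlation 0.6-0.9. The unadjusted analysis was a t-test on cluster proportions (10 df). The adjusted analysis was a logistic model on recruitment HAZ, ignoring arm, followed by a t-test on cluster mean residuals.

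| Persistence of union-council levels | Unadjusted power | Adjusted power |
|---|---|---|
| 0.8 | about 41-46% | about 64-84% |
| 0.5 | about 41-46% | about 52-57% |
| 0 | about 41-46% | about 4-8 points lower than unadjusted |

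Type I error was near 5%.

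**The case against.** **The protocol does not say that prevalent cases count.** A reader might infer that children already stunted at entry are declared outcome events. No sentence says so, and none says the opposite. If risk means new cases, the share above does not apply. But then only about 459-504 of the 900 younger children and 561-616 of the 1,100 older ones would be at risk (49% and 44% stunted at entry), and the sample-size section makes no such reduction. The point is therefore conditional on a final-round comparison among all children.

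**Endpoint prevalence is a legitimate measure here.** The programme is offered to every child, the Methodology section speaks of effects on prevalences, and recovery is a benefit. This stands. The fix below keeps final-round stunting as the outcome, so children who stay stunted still count as events. What changes is the adjustment and the supporting breakdown.

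**There is no bias.** Randomisation balances entry stunting in expectation, and a valid cluster-level standard error already reflects chance imbalance. This stands too. A reader might also infer that an imbalance at entry passes almost whole into the result; the carry-through fractions do not support that.

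**The share cannot be derived from the documents.** It needs assumed recovery and incidence rates or an assumed HAZ correlation. The 44% and 49% describe under-fives or a survey assumption, not children of 6-18 months. In the cohort followed from pregnancy the share is zero by construction.

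**Adjustment may be left to a statistical analysis plan, and HAZ velocity is a secondary outcome.** Both are fair. The data analysis section's reference to multivariate methods leaves room for adjustment. These points lower the severity, but they do not remove the gain from recruitment height or supply a definition that uses entry status.

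**Conclusion.** The concern holds in a limited form. For the two directly recruited child cohorts, the primary outcome makes no use of stunting status at recruitment, although height is measured then. Under an unadjusted final-round comparison, a majority of events probably predate the trial: about 65-95% at 44-49% entry prevalence, and down to 50% at an entry prevalence of 30%, under the assumed rates. The 5-point standard deviation of the entry difference rests only on the protocol's 49%, its ICC and its cluster sizes. The power gain depends on how far union-council stunting levels persist over the year, which the protocol does not tell us. It is substantial at 0.5-0.8, and turns into a loss of about 4-8 points if they do not persist at all.

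The consequence is lost precision and a result that cannot separate prevention from recovery. It is not bias. The low unadjusted power is mainly a sample-size matter and should not be charged to this point. The change is a cheap improvement, not a must-fix.

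**What to change.** Amend the Primary Outcome Measure and Data Analysis sections along these lines: for the two directly recruited child cohorts, stunting (HAZ below -2) at the final round is compared between arms at cluster level, adjusted for HAZ and age at recruitment. New stunting among children not stunted at entry, and recovery among those stunted at entry, are reported by arm as supporting results. Leave the cohort born to recruited pregnant women outside this adjustment, and state in the sample-size section the control risk that goes with the chosen definition.

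The cost is about one paragraph of wording and no new data. A simple rule, fixed in advance, is needed for children with no recruitment height. The price to accept is a few points of power (about 4-8 in simulation) if union-council levels do not persist over the year.
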